#### Data collection for Aims 3a and 3b

*For Aim 3a,* each patient and family member independently rated the helpfulness of each intervention component via a 15-item Likert-type scale at 6 and 12 months after the completion of the **HF**-FamPAL**home**CARE intervention. The participants will rate their agreement with statements, with response options ranging from 1 (strongly disagree) to 5 (strongly agree). Sample statements include *“The nurse and volunteer prepared me for home HF care,” “I was comfortable during the discussion with the nurse/visitor,”* and *“I know ways to reduce breathlessness.”* Descriptive analysis will be used to evaluate the responses on the helpfulness scale. The nurse interventionists and visiting volunteers will rate the same helpfulness scale at 6 and 12 months following the **HF**-FamPAL**home**CARE intervention.

*Aim 3b: Focus group data collection.* The Principal Investigator (PI) and Co-Investigator (Co-I) are experienced in focus group research methods and working with families managing HF [47]. We will conduct 4 to 6 focus groups across West Virginia counties, each consisting of 3 to 5 rural stakeholders, such as church leaders, patients, and caregivers. These sessions will be held at rural sites, with the option of using a secured ZOOM for recording encrypted discussions and enabling participation from other rural leaders.

The PI and Co-I will facilitate discussions, starting with questions such as *“How can we collaborate to develop a 10-year plan for maintaining rural volunteers and continuing home care implementation?”* and *“What are the facilitators of and barriers to sustaining the HF-FamPALhomeCARE intervention in rural Appalachia?”* The same broad questions with prompts will guide all focus group discussions. The PI and Co-I will observe group dynamics to ensure that everyone participates and will ask probing questions for clarification and deeper insights.

The discussions will be audiotaped and transcribed, ensuring that no individual participants’ identities are disclosed. Each session will last approximately 60 to 90 min. Data saturation is achieved when no new topics emerge, with experts indicating that 99% of all new concepts typically emerge by the 20th participant [48]. All group data will be transcribed together.

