## Methods/design

### Aims

The aims of this RCT are to test the outcomes of the **HF**-FamPAL**home**CARE bundled intervention, with patients and family caregivers (104 dyads) managing home supportive EOLPC for end-stage HF in rural WV. The specific aims and hypotheses, with outcome measures for this RCT, are listed in Table 1.

**Table 1 Tab1:** Specific Aims, Hypotheses, with the Outcome Measures for this RCT

**Primary Aims** are to test the outcomes of the **HF**-FamPAL**home**CARE bundled intervention, with patients and family caregivers managing home supportive EOLPC for end-stage HF in rural WV
**Aim 1:** Compared to the control group at 3, 6, 9 months, and 1-year follow-up:
***Hypothesis 1a.*** The patients in the intervention group will have higher scores on HF-related health quality-of-life measure and on the functional health well-being scale
***Hypothesis 1b.*** The family caregivers in the intervention group will have higher scores on the functional health well-being scale
**Aim 2:** Compared to the control group at 3, 6, 9 months, and 1-year follow-up:
***Hypothesis 2a.*** The patients in the intervention group will have (a) lower depression and anxiety scores and (b) higher numbers of signed EOL advance directives
***Hypothesis 2b.*** The family caregivers in the intervention group will have (a) lower depression and anxiety scores, (b) lower home caregiving burden scores, and (c) improved home HF EOLPC preparedness and improved home palliative care scores
**Secondary Aim** (Aim 3) is to assess the bundled intervention helpfulness, cost, and the plans for maintaining the sustainability of our faith community nurses and visiting volunteers engagement across rural WV
***Aim 3a.*** Compare the bundled intervention helpfulness questionnaire ratings by the patient, family caregiver intervention group participants, and the interventionists (faith community nurse and visiting volunteers). Determine the implementation cost of the **HF**-FamPAL**home**CARE bundle
***Aim 3b.*** Using focus group research, determine 10-year plans for sustaining the bundle implementation, maintaining rural volunteers and coordinating administrative aspects of the program

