##### Data analysis for Aim 3a

A descriptive analysis will be used to summarize the responses to the helpfulness scale items. Statistical assumptions will be tested to determine whether to use analysis of variance (ANOVA) or the Kruskal‒Wallis test for comparing mean scores between four groups: patients, caregivers, and interventionists (faith community nurses and visiting volunteers). Interventionists will also use anecdotal notes to report topics brought up by families that require reinforcement. These topics will be tabulated and reported to improve the intervention.

To determine the cost of the **HF**-FamPAL**home**CARE intervention implementation, all charges related to implementation are calculated. The items include the costs of personnel time for training and administering each discussion session, the materials, home/clinic visit travel, and telephone and mailing costs. Research costs related to data collection and material photocopying will be totaled and reported as study costs. The average intervention implementation cost across all families will be calculated and reported [15].

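### Nurses and volunteers are to complete a helpfulness scale whose published items are worded for recipients, so the four-group comparison of means cannot show whether families and interventionists differ or agree

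*Protocol article*

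**What the plan says.** Table 1 of the protocol article (section Aims) sets the ratings part of Aim 3a: "Compare the bundled intervention helpfulness questionnaire ratings by the patient, family caregiver intervention group participants, and the interventionists". The same aim also covers the cost of implementation.

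The section Data collection for Aims 3a and 3b says that patients and family members rate the intervention "via a 15-item Likert-type scale at 6 and 12 months", with five response options from strong disagreement to strong agreement. It gives three sample items:

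- "The nurse and volunteer prepared me for home HF care"
- "I was comfortable during the discussion with the nurse/visitor"
- "I know ways to reduce breathlessness"

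It then states: "The nurse interventionists and visiting volunteers will rate the same helpfulness scale at 6 and 12 months".

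The section Data analysis for Aim 3a plans descriptive summaries of the items. It also plans ANOVA or Kruskal-Wallis, chosen after checking assumptions, for "comparing mean scores between four groups: patients, caregivers, and interventionists (faith community nurses and visiting volunteers".

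One other place describes the instrument. The section Data collection for Aims 1 & 2 says that interventionists and intervention-group participants fill in separate, anonymous helpfulness scales at 6 and 12 months. It does not say whether separate means a different form or the same form completed apart.

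**The concern.** A comparison of means between rater groups assumes that a given score carries the same meaning whoever gives it. The sample items are in the first person of a recipient, and in two of them the nurse or visitor is the person being rated. If deliverers answer the same items, a 4 from a nurse and a 4 from a caregiver are not two readings of one quantity.

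What is at stake is the family-versus-interventionist part of Aim 3a. A significant result could come from item meaning alone. A non-significant one could hide real disagreement about how helpful the bundle was. Neither the choice between ANOVA and Kruskal-Wallis nor the planned check of assumptions would reveal this, because both concern the distribution of scores and not what they measure. The problem would remain even if every rating were statistically independent.

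**Working it through.** The plan states no sample size, power or alpha for Aim 3a, so there is no figure to reproduce. The check is a reading of the items by rater, followed by a simple bound on the effect on the score.

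**Items by rater**

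| Sample item (topic) | Answered by a patient or caregiver | Answered by a nurse or volunteer |
|---|---|---|
| Being prepared for home care by the nurse and volunteer | Rates the deliverers' preparation of the respondent | Self-referential: the respondent is one of those doing the preparing |
| Comfort in the discussion with the nurse or visitor | Rates how the session was received | Comfort with a colleague or with oneself |
| Knowing how to relieve breathlessness | Can reflect what was learned | For a nurse, professional knowledge; for a volunteer, background or training |

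All three items change meaning or lose it when a deliverer answers. They are 3/15 = 20% of the scale. The other 12 items are not shown.

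**The two descriptions of the form**

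- If the forms are identical, as the Aim 3a data-collection section says, the table above applies.
- If the forms differ, as the section for Aims 1 & 2 may mean, the two sections conflict, and the article does not show the common measure that the four-group test needs.

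The comparison is unsupported on either reading.

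**Illustrative size**

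Take the score as the mean of the 15 items, each scored 1 to 5. Let k be the number of items that mean something different for interventionists, and d the resulting difference per item in points. Then

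shift in group mean = (k / 15) × d

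| k | d = 0.5 | d = 1 |
|---|---|---|
| 3 (only the items shown) | 3/15 × 0.5 = 0.10 | 3/15 × 1 = 0.20 |
| 15 (all items) | 15/15 × 0.5 = 0.50 | 15/15 × 1 = 1.00 |

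The values of d, any k above 3, and the scoring as an item mean are assumptions. The sign of d is not known.

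**The case against.** The strongest reply is that the article condenses a fuller protocol. Its own description of separate scales may mean that an adapted interventionist form already exists, and three samples out of 15 do not characterise a whole scale. Part of this stands. The exact wording that interventionists will see is not settled, and nothing establishes that all 15 items measure something different for deliverers. It does not clear the plan, because the sentence about using the same scale is an affirmative statement and not an omission. If the forms do differ, the basis for comparing mean scores is still not given.

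Four stronger readings are tempting, and the document does not support them:

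- *Aim 3a cannot be answered.* The patient-versus-caregiver contrast, the descriptive item summaries and the costing do not need deliverers' scores to be comparable with families' scores.
- *Self-ratings by deliverers will make the bundle look more helpful.* No pooling of rater groups is planned, so deliverer scores would appear as their own groups. The document gives no evidence that they would be higher.
- *The artefact would shape the sustainability plan.* Under Data analysis for Aim 3b, themes come from coded focus-group transcripts and are then compared with the helpfulness ratings among other sources. The ratings do not generate the themes.
- *Most of the pairwise comparisons are spoiled.* Of the six possible pairs, five include a deliverer group, but one of those five is nurse versus volunteer. The plan names an overall test and lists no pairwise tests, and a count of pairs does not measure bias.

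It is also fair to say that this is one part of a secondary, largely descriptive aim, and that no stated decision depends on the test.

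**Conclusion.** The point holds for the contrast between families and interventionists. As written, the plan gives both the same scale, every published item is worded for a recipient, and the means are then tested across all four groups. Neither a difference nor a lack of one between families and interventionists can be interpreted as disagreement or agreement about helpfulness.

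The size cannot be fixed from the document. Under the stated assumptions, item meaning alone would account for 0.10 to 0.20 points on a 1-to-5 mean if only the three shown items are affected, and for up to 0.50 to 1.00 if all 15 are.

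The conclusion rests on the sentence about the same scale being meant literally. If an adapted form exists, what remains is a conflict between two sections and a comparison of means on an undocumented common measure. The primary aims are not touched. The change is worth making because it is cheap and the four-group test is the only inferential analysis named for the helpfulness ratings.

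**What to change.** 1. Reconcile the two data-collection sections, and state whether interventionists receive the identical items or an adapted form.
2. Give nurses and volunteers a parallel version worded for deliverers. The first sample item, for example, could ask whether the dyad was ready for home HF care by the end of the sessions.
3. In Data analysis for Aim 3a, limit the inferential comparison of the recipient scale to patients versus caregivers.
4. Set the interventionist ratings beside the family ratings descriptively, item by item. This keeps the comparison named in Table 1 without a four-group test of means.

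The cost is one reworded 15-item form and a few changed sentences, with no added participants or visits. The single four-group test is lost.

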### Data analyses

All the outcome measures have established discriminant or construct validity, internal consistency, reliability, and specificity. Each has been used with diverse populations, chronic illness patients, and HF families. These measures have been shown to distinguish clinically significant differences and are responsive to changes over time. These questionnaires were easily completed within 30 min. The sample demographics will be tabulated and reported.

#### Data analysis for Aims 1 & 2

Our experienced statistician will employ hierarchical generalized linear models with repeated measures to identify significant differences in outcomes between groups and to control for nested dyadic analysis [49]. The models will include fixed effects of treatment, time, and the treatment‒time interaction. Patient and family caregiver effects will be treated as random to account for dependence among repeated observations on the same subject as well as among subjects within the same family [37]. These models detect changes in outcome variables over time, differences between groups, and within-group differences over time. The SAS Proc MIXED procedure will be utilized. General linear modeling using linear contrasts of selected model parameters will test for significant differences. Point estimates and confidence intervals will be produced via contrasts and estimates of appropriate linear combinations of model parameters. The overall experimental error rate will be controlled via the Bonferroni procedure for multiple testing.

Multicollinearity among study variables will be determined and statistically controlled for in the data analysis. The number of mental health visits (for severe anxiety and depression) will be tracked for comparison between groups. To assess differences in HF EOLPC decisions, the number of family members and patients who sign an advance directive form, reveal a decision, or identify someone to help with HF EOLPC options will be recorded and reported. The proportion of patients signing an advance directive form will be used to evaluate the acceptability of EOLPC discussions. Subjects’ outcomes will be recorded at the time of death or 12 months postintervention, whichever comes first.

#### Data Analysis for Aim 3

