#### Randomization

The consulting statistician will use computerized randomization to generate numbers for subject enrollment. Two separate randomization lists will be created: one for males and one for females. Families will then be randomly assigned to either the control or intervention group at a 1:1 ratio. The group assignments are placed in sealed envelopes according to sex. Our RCT design adheres to CONSORT standards and rigorous research procedures [30]. The study is designed to enhance both internal and external validity, making it suitable for detecting differences between groups in behavioral intervention trials [31].

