#### Sample size

The power and sample size determination is based on a preliminary RCT, which revealed a moderate effect reduction in the burden of caregiving and improvements in patients’ HF-related health status [15]. With the use of G*Power v.3.1.9.7 for repeated-measures ANOVA with α = 0.05, Cohen’s d = 0.25 (moderate effect size), a power of 80%, two groups with 5 measurements, and correlations among repeated measures (0.50), a *sample size of 86 family dyads* will be needed. Our power analyses performed by this study’s statistician indicate that this sample size is sensitive enough to detect a significant difference in the study outcomes with this repeated measure design [36].

Our biostatistician’s revised precision calculation for linear mixed model analysis was based on the effect size outcomes of our HF palliative care studies. To account for an expected 20% attrition (many due to HF-related deaths), eight additional families will be recruited for each group. The calculated sample size was 86 patients, with an additional n = 18 for the expected 20% attrition rate (total sample N = 208; 104 patients and 104 caregivers) for this study. In this analysis, the random and fixed effects and quarterly repeated measures also add power.

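### As listed, the Aim 1 and 2 model uses baseline inefficiently, omits the sex stratum, and has no term giving separate patient and caregiver effects on the scales they share

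*Protocol article*

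**What the plan says.** All places are in the Protocol article.

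- **Fixed effects (Data analysis for Aims 1 & 2).** "The models will include fixed effects of treatment, time, and the treatment"-by-time interaction. No other fixed effect is named.
- **Random effects (same section).** "Patient and family caregiver effects will be treated as random to account for dependence among repeated observations on the same subject". The sentence then extends this to dependence between the members of one dyad. The stated purpose of the hierarchical model includes "to control for nested dyadic analysis".
- **Tests (same section).** Estimates and intervals come from "contrasts and estimates of appropriate linear combinations of model parameters", with a Bonferroni correction.
- **Baseline (Sample size; Data collection for Aims 1 & 2).** The calculation assumes "two groups with 5 measurements". The five occasions are baseline and 3, 6, 9 and 12 months, so baseline is one of the responses.
- **Stratification (Design/methodology; Randomization).** The design is stratified by sex: "Two separate randomization lists will be created: one for males and one for females".
- **Hypotheses (Table 1).** These are separate by role. Functional health appears for patients in 1a and for caregivers in 1b ("The family caregivers in the intervention group will have higher scores on the functional health well-being scale"). Depression and anxiety appear for patients in 2a and for caregivers in 2b.

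**The concern.** The article specifies a model, and that model does not fit the trial's own design in three respects.

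1. **Role.** Table 1 makes separate claims about patients and caregivers on three shared constructs. If both dyad members enter one model whose fixed effects are treatment, time and their interaction, every treatment contrast is common to both roles. Random subject and family effects handle dependence; they do not supply a treatment effect for each role.
2. **Baseline.** A baseline score that enters only as a response is used either not at all (a between-arm difference at a follow-up visit) or as a simple change. At the correlation the plan assumes, both waste information that has already been paid for.
3. **Sex.** The factor that governed allocation is not in the analysis, so the standard error does not credit the stratification.

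At stake are precision, in a trial of modest size that will also divide its error rate by Bonferroni, and whether the estimates on shared scales answer the hypotheses as written.

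**Working it through.** **Inputs from the document.** Correlation among repeated measures ρ = 0.50, five occasions (one baseline, four follow-ups), α = 0.05, stated effect size 0.25 (labelled Cohen's d), and 86 dyads before attrition, hence 86/2 = 43 per arm.

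**Assumptions.** Equal correlation between all occasions, unit SD, complete data, two-sided test, no Bonferroni.

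**The plan's own figure.** The document gives no precision figure for the model terms; its only related figure is the 86 dyads. For a between-groups repeated-measures test, λ = N·f²·m/(1+(m−1)ρ). With f = 0.25 and m = 5 this is N × 0.0625 × 5/3. Power reaches 80% at N = 78, and is 84.1% at N = 86. So 86 is not reproduced from the stated inputs. That is a separate matter; here 43 per arm serves only as the planned size.

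**Step 1: variance factor v for each contrast.** The between-arm SE is proportional to √v.

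| Contrast | Post-only | Change from baseline | Baseline-adjusted |
|---|---|---|---|
| One visit | 1 | 2(1−ρ) = 1.00 | 1−ρ² = 0.75 |
| Mean of four follow-ups | (1+3ρ)/4 = 0.625 | 0.625+1−2ρ = 0.625 | 0.625−ρ² = 0.375 |

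At ρ = 0.50, post-only and change contrasts have the same variance, so the gain from adjustment is the same against either.

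- One visit: √0.75 = 0.866, an SE 13% smaller.
- Follow-up mean: √(0.375/0.625) = 0.775, an SE 23% smaller.

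**Step 2: sensitivity to ρ.** For one visit against the change contrast, the variance falls from 1.40 to 0.91 (35%) at ρ = 0.3 and from 0.60 to 0.51 (15%) at ρ = 0.7. Against post-only, it falls from 1 to 0.91 (9%) and from 1 to 0.51 (49%).

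**Step 3: power with 43 per arm.** Noncentral t, 84 df, noncentrality (d/√v)·√(43/2).

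| Assumed d | Contrast | Unadjusted | Baseline-adjusted |
|---|---|---|---|
| 0.50 | One visit | 63% | 75% |
| 0.50 | Follow-up mean | 83% | 96% |
| 0.25 | One visit | 21% | 26% |
| 0.25 | Follow-up mean | 31% | 46% |

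A normal approximation gives 47% for the last cell. The value d = 0.50 is an assumption: it corresponds to f = 0.25 in two equal groups (d = 2f), whereas the article labels 0.25 as d. Both are therefore shown.

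**Step 4: sex.** The document gives no figure. If sex explains an assumed 1% to 5% of outcome variance, the SE ratio is √0.99 = 0.995 to √0.95 = 0.975, a gain of about 0.5% to 2.5%.

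**Step 5: role.** Take a shared scale with an assumed effect of 0.5 SD in patients and 0 in caregivers, in equal numbers. A common treatment contrast estimates (0.5 + 0)/2 = 0.25 SD, which is neither the patient effect nor the caregiver effect. No linear combination of treatment, time and treatment-by-time parameters recovers the two separately.

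**The case against.** The strongest reply is that this is a condensed article. It says what the models will include and never says the list is complete, so covariates, stratum terms and the handling of baseline may sit in a fuller document. That stands as a limit: one cannot conclude that these terms are excluded, only that the published specification does not contain them.

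Baseline is also not ignored. With baseline as a level of time, the interaction yields change from baseline, which is an accepted longitudinal analysis. True, but at ρ = 0.50 the change contrast has exactly the post-only variance, so this does not remove the loss.

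Several stronger readings are tempting and are not supported:

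- **A diluted treatment effect.** A reader might infer that the test is the treatment main effect averaged over all five visits, so that baseline dilutes the effect to four fifths. The plan names no such test. Table 1 places the comparisons at 3, 6, 9 and 12 months, and the analysis section refers to selected contrasts.
- **Deliberate pooling of roles.** No passage says that one common effect will be estimated. The hypotheses are separate, and data are collected separately from each role. Pooling cannot arise for heart-failure quality of life (patients only) or for burden and preparedness (caregivers only). What stands is that no listed parameter delivers the separate effects on shared scales.
- **Bias or invalid inference.** Omitting baseline or sex leaves the randomised comparison unbiased. Omitting the stratum makes the standard error slightly conservative.
- **An undefined stratum.** The article does not say whose sex selects the list for a mixed-sex dyad. That is an allocation detail a fuller protocol may give, not an error in this model.

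**Conclusion.** The point holds as a mismatch between the model as listed and the design, and it is worth correcting.

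- **Role** is the most substantive part. For functional health, depression and anxiety, the listed fixed effects cannot yield the role-specific effects claimed in Table 1. This rests on reading the within-family dependence clause as one joint model for those scales. If separate models are intended, a sentence saying so settles it.
- **Baseline** is a loss of efficiency: 13% of the SE at one visit and 23% for the follow-up mean, under equal correlations of 0.50. The power gains depend on an assumed d, and neither the follow-up mean nor any single visit is named as the primary contrast. Bonferroni would lower all the power figures.
- **Sex** matters little numerically. The reason to include it is consistency with the randomisation.

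**What to change.** Replace the fixed-effects sentence with a specification along these lines:

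- Outcomes are the 3, 6, 9 and 12 month scores. Fixed effects are treatment, visit, treatment by visit, baseline score by visit, and the sex stratum as used in the randomisation. Alternatively, keep baseline as a response in a model that constrains the arms to a common baseline mean, with the sex stratum included.
- For functional health, depression and anxiety, either fit patients and caregivers in separate models, or add role and its interactions with treatment and visit to the joint model.
- Report treatment contrasts by role at the follow-up visits, so that each estimate maps to 1a, 1b, 2a or 2b.

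The cost is wording only: baseline scores, sex and role are already collected, and neither the sample size nor the visit schedule changes.

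### The plan promises generalized linear models for Aims 1 and 2 but names only PROC MIXED, which cannot fit the yes/no advance-directive outcome of Hypothesis 2a as a binary outcome

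*Protocol article*

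**What the plan says.** Table 1 in the Aims section lists, for patients under Hypothesis 2a, "higher numbers of signed EOL advance directives". The comparison is set out as "Compared to the control group at 3, 6, 9 months, and 1-year follow-up".

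The Data analysis for Aims 1 & 2 section gives one analysis for both aims. It begins with "hierarchical generalized linear models with repeated measures to identify significant differences in outcomes between groups", naming no distribution or link. Fixed effects are treatment, time and their interaction; patient and caregiver effects are random. Then come "The SAS Proc MIXED procedure will be utilized" and "General linear modeling using linear contrasts of selected model parameters will test for significant differences". No other procedure is named for these aims. A later paragraph of the section says that "the number of family members and patients who sign an advance directive form, reveal a decision, or identify someone to help" with end-of-life options will be recorded and reported, and that the proportion of patients signing will be used to judge acceptability. It names no between-group test for that proportion.

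**The concern.** The model class and the procedure disagree. A hierarchical generalized linear model could carry a binomial distribution with a logit link; PROC MIXED and general linear contrasts cannot. For the questionnaire scores this does no harm. For the directive it leaves a hypothesis under the Primary Aims with a test built for another kind of outcome, or with none.

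It could matter because directive status is cumulative: once signed, it normally stays signed. Repeated 0/1 values of this kind are strongly correlated between adjacent visits and less so between distant ones. A random intercept imposes one correlation on all pairs of visits. Contrasts over the whole follow-up may then get standard errors that are too small.

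**Working it through.** **No planned figure to reproduce.** The Sample size section powers a repeated-measures ANOVA and gives nothing for the directive. The rates below are therefore assumptions, shown as ranges.

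**Inputs from the article.** 52 patients per arm; visits at baseline, 3, 6, 9 and 12 months; random subject effects; treatment, time and interaction.

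**Assumptions.** Proportion b signed at baseline, 0 to 60%. Proportion q of the others signing by 12 months, 20 to 40%, equal in both arms (the null), with the same hazard in each quarter. Complete data. A random intercept as the only source of correlation.

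**Formula.** The quarterly hazard is h = 1 − (1 − q)^(1/4). The proportion signed at visit t (t = 0 to 4) is p_t = 1 − (1 − b)(1 − h)^t. For cumulative status, the covariance between visits s ≤ t is p_s(1 − p_t). A random-intercept fit estimates residual variance as average variance minus average covariance. It takes the variance of a patient's 12-month-minus-baseline change as twice that.

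**Worked case, b = 0 and q = 0.40.**
- h = 1 − 0.60^(1/4) = 0.1199, so p_t = 0, 0.1199, 0.2254, 0.3183, 0.40.
- Average variance 0.1474; average covariance 0.0726; residual variance 0.0748.
- Variance of the change as the model sees it: 2 × 0.0748 = 0.1496. True variance: 0.40 × 0.60 = 0.24. Ratio 1.60, square root 1.267.
- The nominal 1.96 acts as 1.96/1.267 = 1.547, so the two-sided rejection rate is about 0.122.

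For b = 0.40 and q = 0.20 the ratio is 1.90 and the rate about 0.155.

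**Simulation under the null.** 52 per arm; 10,000 trials per setting; b of 0, 10, 20, 40 and 60%; q of 20, 30 and 40%.

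| Test at nominal 0.05 | Rejection rate |
|---|---|
| 12-month-minus-baseline contrast, random intercept | 0.121–0.164 |
| Treatment-by-time test, random intercept | 0.071–0.084 |
| Time-averaged group effect, random intercept | 0.047–0.056 |
| 12-month-minus-baseline contrast, unstructured covariance | 0.047–0.056 |
| 12-month visit tested on its own | 0.049–0.058 |

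Smaller runs of 2,000 trials at 43 and 52 per arm gave 0.125–0.180 for the first row and 0.069–0.088 for the second. Exact calculation for a t test at one visit, at 43 or 52 per arm, gave 0.043–0.059.

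One qualification: if the 12-month difference is read off the random-intercept model instead of tested separately, its rate depends on b. It is about 0.12 to 0.14 at b = 0, about 0.09 at 10%, 0.06 to 0.07 at 20%, and 0.03 to 0.06 at 40 to 60%.

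**Bonferroni does not repair this.** If four tests are assumed, the nominal level is 0.05/4 = 0.0125 (z = 2.498). In the worked case 2.498/1.267 = 1.971, a rate of about 0.049, or 3.9 times nominal.

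**The case against.** The strongest reply is that the section does name generalized linear models, so the statistician may intend a suitable one and the procedure name may be shorthand for the continuous scores. A condensed article may also leave per-outcome detail to a fuller plan. This limits the point to an inconsistency and does not remove it: the article chose to name a procedure for both aims, and that procedure does not do what the preceding text promises.

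The second reply is that a Gaussian analysis of 0/1 data is often harmless. This stands in part. Single-visit tests and the time-averaged effect hold their size, and Hypothesis 2a is worded visit by visit. PROC MIXED can also fit an unstructured covariance, which restores the change contrast. The inflation belongs to a random-intercept-only fit; the article describes random effects but fixes no covariance structure.

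A reader might infer more, and the article does not support it:
- *That directives signed before baseline are counted as events.* No section says so. The wording about those who sign can mean new signing, and data are collected at baseline. Any dilution would need a prior-signing rate that the article does not give, would vanish at zero, and under randomization would cost power without favouring either arm.
- *That PROC MIXED must assume constant variance over visits.* It can fit a separate variance at each visit.
- *That mental health visits are wrongly assigned to it.* They appear in no Table 1 hypothesis, and a separate paragraph says only "The number of mental health visits (for severe anxiety and depression) will be tracked for comparison between groups".

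**Conclusion.** The point holds as a contradiction between the announced model class and the only named procedure, for one binary outcome within the Primary Aims. It is worth correcting, but it does not threaten the trial. The excess false-positive risk, about 0.12 to 0.17 for the change contrast and 0.07 to 0.09 for the treatment-by-time test, is conditional on a random-intercept-only covariance, complete data and the assumed signing rates. Without those conditions the mismatch remains, but its size cannot be stated from the article.

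**What to change.** Keep PROC MIXED for the continuous scores. For the patient advance directive, name a binary model at 3, 6, 9 and 12 months, for example PROC GLIMMIX or GEE with a binomial distribution and a stated link. Either adjust it for directive status at baseline or define the outcome as newly signed after baseline. Adjust also for sex, the stratification factor in the Randomization section.

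Two practical points bear on the choice. If a signed directive is taken to stay signed, everyone signed at baseline is a yes at every visit. A logit model adjusted for baseline status then has a separated covariate, so analysing new signing among those without a directive at baseline is easier to fit. For a cumulative status, GEE with robust standard errors also avoids relying on a random intercept for the correlation.

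The cost is analysis wording, plus recording directive status at baseline for every patient. That item is not named among the baseline examples, although the list is open-ended. Restricting to patients without a prior directive reduces the denominator.
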